### Interventions

#### Investigational drug

The intervention which will be evaluated in this trial is the intake of dexamethasone. In Austria the tablets are provided in capsules of 4 mg each and are taken orally before 8.00 in the morning. The daily dosages are 16 mg at days 1 and 2, 12 mg at days 3 and 4, 8 mg at day 5, and 4 mg at day 6. In China there are only tablets of 0.75 mg dexamethasone available, so capsules are filled with six, four or three tablets. The following dosages can be obtained: 15.75 mg at days 1 and 2; 12 mg at days 3 and 4; 8.25 mg at day 5 and 4.5 mg at day 6. This intervention will be compared against placebo.

#### Comparative drug

Matching oral capsules are filled with maltodextrin to the same weight and are administered similarly.

#### Concomitant care

All patients in the study will receive the routine standard of care. This will include a check of blood and vital parameters, a neurologic investigation and CT scan at admission. An acute onset of neurologic deterioration or a decline of alertness will need an urgent operative treatment. For neurosurgical procedures normal coagulation parameters are essential. In warfarin medication, the international normalized ratio (INR) has to be normal prior to surgery. Coagulation factors or other blood products will be administered as required. ASS is to be stopped five days and GpIIb/IIIa-receptor antagonists seven days before surgery, and NOAC a duration longer than double of their pharmacological half-life. Only those patients are eligible who are able either to pause their anticoagulant or antiplatelet medication, or to tolerate a conversion to LMWH (low molecular weight heparin) for two weeks postoperatively.

In consideration of different techniques available for the evacuation of a chronic subdural hematoma, the following procedure has been agreed: one burr hole over the site of the hematoma, no irrigation and a closed drainage system. The drain will be continued up to 48 hours. Criteria for discontinuing before 48 hours are air in the system, an incorrigible flow arrest or delivery of pure CSF.

Pain will be treated according to the WHO guidelines
[29].

LWMH are used for deep venous thrombosis prophylaxis. The application has to start within 24 hours postoperatively, or if the patient is mobile, less than 3 hours a day. Daily neurologic investigations and control of vital parameters and wound healing will be added to standard care, as will concerted medication and drawing of blood samples, CT scans and physical therapy as necessary.

There will be a focus on hyponatremia and pathologic INR values. Patients who received oral anticoagulation preoperatively will need to be controlled daily and will have to have their parameters kept within the normal range throughout the hospital stay. The same procedure will be applied in hyponatremia. At study day-3 blood glucose levels are evaluated. At a level higher than 300 mg/dl the patient will be excluded from the trial. In order to detect a raised intraocular pressure a measurement will be performed during the treatment period.

Participants will remain inpatients until the study drug is administered completely. Patients who ready to be discharged home earlier will have to finish the medication on their own. Protocol-mandated assessments will be performed according to the table of assessments (Table 
2). CT and/or MRI scans will be sent to a core laboratory and evaluated centrally in a triple-blinded way. Blood samples will be analyzed by the investigational laboratory locally.

**Table 2 T2:** Visit and assessment schedule

**VISITS**	**Screening**	**Post-procedure**	**Day 2 post operation**	**Day 3 of drug protocol**	**Until hospital discharge**	**Week 4 (16±7 days)**	**Week 12 (48±7 days)**	**Week 24**^ **1** ^**(96±7 days)**
Informed consent	x							
Medical history/demographics	x							
Procedure related information	x							
Randomization	x							
Concomitant medications^2^	x	x	x	x	x	x		
Physical examination	x				x			
Hematology, biochemistry, coagulation^3^	x				x(OD)^4^			
Urine pregnancy test	x							
Markwalder score	x				x (OD)	x	x	x
Blood glucose				x				
Intraocular pressure					x			
Neurological worsening events					x	x	x	
CT scan	x^5^		x^6^			x	x	x
Post-discharge information						x	x^7^	x
Adverse events			x	x	x^8^			
Serious adverse events	x^9^	x^9^	x	x	x	x	x^10^	

OD=once a day.

CT=computer tomography.

^1^Only in case of reoperation.

^2^Concomitant medications will be recorded in the CRF from 2 weeks prior to study drug start and up to the end of study drug medication.

^3^Blood will be analyzed locally and the results will be recorded in the CRF.

^4^Preoperative oral anticoagulated patients need a coagulation monitoring once a day to keep the parameters normal. In the same way are patients monitored with hyponatremia.

^5^If the baseline CT scan performed at a referral center, is of acceptable quality, and is available at the investigational site at the time of screening, it does not need to be repeated. However, if the only baseline CT scan available is a hardcopy film, then it must be repeated at the investigational site.

^6^CT scan to be performed during 48h post operation. In case of neurological worsening CT scans are repeated as required.

^7^At week 12 the patient will return to the hospital for documentation of his/her residence (e.g. home, rehabilitation centre etc.), any new hospitalizations or surgical procedures (directly or indirectly related to the cSDH) since the first hospital discharge, and to ensure that ongoing AEs/SAEs or new SAEs are followed up/documented. In case of reoperation the same procedure is performed at week 24.

^8^AEs reporting and follow-up: Reporting of all new AEs up to one day after study drug discontinuation; follow-up of ongoing AEs only thereafter.

^9^SAEs related to study-mandated procedures after signature of informed consent and before study drug administration.

^10^Serious adverse events still ongoing at the Study Completion visit must be followed until resolution or stabilization or until the event is otherwise explained. New SAEs occurring at any time after the 21-day follow-up period after study drug discontinuation may be reported to the Sponsor within 24 hours of the investigator´s knowledge of the event, if felt appropriate by the investigators.

Two regular follow-up visits are planned. At weeks 4 and 12 after the operation a CT scan and clinical investigation are performed. Only in the case of reoperation is another visit necessary as an outpatient at week 24.

Concomitant medications will be proton pump inhibitors, vitamin K and anticonvulsants as required. In addition participants will have to avoid traditional medicines (that is, plant-, animal- or mineral-based medicine, such as traditional Chinese medicine).

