### Exclusion criteria

The exclusion criteria are: 1) pregnancy and nursing; 2) diabetes; 3) hypertension (systolic blood pressure (SBP) >180 mmHg) that is refractory to treatment; 4) glaucoma; 5) Known hypersensitivity to dexamethasone; 6) known peptic ulceration; 7) acute systemic infection (fever, leucocytosis, elevated C-reactive protein (CRP) and/or PCT (Procalcitonin); 8) parasitic infection; 9) current or previous history of severe affective disorders (especially previous steroid psychosis); 10) recent myocardial infarction (as myocardial rupture has been reported); 11) patients for whom study drug cannot be started within 48 hours after evacuation of the hematoma; 12) patients for whom it is known at the time of screening that certain follow-up, protocol-mandated imaging assessments will not be feasible; 13) patients unlikely to comply with the protocol (for example, unable to return for follow-up visits); 14) current alcohol or drug abuse, or dependence; 15) use of another investigational product within 28 days prior to randomization; 16) vitamin-K antagonists during the first 2 weeks after operation; 17) GpIIb/IIIa-receptor antagonists, ASS (acetylsalicylic acid) or NOAC (new oral anticoagulants) during the first two weeks after surgery; and 18)reoperation within 48 hours after the first operation.

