### Sample size

Let p_verum_ be the reoperation rate in the verum group and p_placebo_ be the reoperation rate in the placebo group. The null hypothesis H_0_ is that the ratio of both rates p_placebo_ /p_verum_ is equal or smaller than 2, the corresponding alternative hypothesis H_1_ is that the ratio p_placebo_ /p_verum_ is larger than 2. In other words, the alternative hypothesis states that dexamethasone reduces the reoperation rate by 50% or more. For a reasonable medication the effect size is assumed to be this size because dexamethasone will be taken by the majority without benefit.

The assumed reoperation rate p_placebo_ is 10%. This is in accordance with the data from our department and the Chinese study sites. In order to detect a ratio p_placebo_ /p_verum_ of 2 or more with a power of 80%, the sample sizes are n1 = n2 = 370 in each arm. The type I error is 5% and the type II error for this scenario is 20%. The actual power of 83% is based on the exact power for the ratio of two binomial populations, one-sided and based on the score test (StatXact Cytel Software Corporation (2002) *StatXact 6.0 For Windows User Manual*, Cytel Software Corporation, Cambridge MA, USA). Due to possible drop-out of patients, we increased the sample sizes up to 410 in each group. Thus, 820 patients undergoing surgery for cSDH will be included.

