### Data analysis

The primary endpoint is the rate of reoperation between 48 hours and 12 weeks after the initial evacuation of a chronic subdural hematoma. Mandatory reoperation during the first 48 hours is related to surgical complications. In such rare cases the patient will be excluded.

Evaluation of the Markwalder score will be done by computing crosstabulation tables and applying Pearson’s chi-square test. Data will be checked carefully for outliers and for normality based on the Kolmogrov-Smirnov test and Liliefors test. To evaluate the impact of dexamethasone on the thickness of the hematoma and other continuously distributed, metrically scaled variables, mixed models with treatment group as the independent factor and time as the repeated factor will be applied (if all assumptions for the model are met). Linearity will be assessed by Box Tidwell and log transformation. Corresponding planned contrasts together with 95% confidence intervals will be computed. If these variables do not fulfill the assumptions for parametric testing, nonparametric methods such as the bootstrap *t*-test, Kruskal-Wallis analysis of variance (ANOVA) with median tests and Friedman ANOVA with Wilcoxon matched-pairs test will be applied: 95% confidence intervals based on Pearson-Clopper values will be computed to estimate the reoperation rate in both groups. An unconditional test (Barnard’s test for superiority) for the ratio of these two proportions will be used. A *P*-value less than 5% will be considered statistically significant. All analyses will be done by one of the authors (WH) using STATISTICA 10 (Hill, T and Lewicki, P (2011). *STATISTICS: Methods and Applications*. StatSoft, Tulsa, OK, USA), StatXact 6.0 (Cytel Software Corporation (2003) Cytel Software Corporation, Cambridge MA, USA), NCSS 8 and PASS 11 Hintze, J (2012), NCSS 8, NCSS, LLC, Kaysville, UT, USA. (http://www.ncss.com).

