### Methodology

The DRESH study has a straightforward design: on the one hand an efficient concomitant treatment which should be evaluated to the highest evidence possible, and on the other hand the study dependent measures are perfectly integrated into the clinical routine. In the light of this aspect three points are worth mentioning: a clear study design and statistics, waived SAEs and a maximal time frame for randomization. Even patients who undergo emergency surgery can be randomized postoperatively. Most of the exclusion criteria are due to the use of dexamethasone or anticoagulant drugs. There is a simple primary endpoint defined without any surrogate parameter: reoperation. The reoperation rate should be decreased by 50%, because only 82 patients out of 820 (assumed reoperation rate of 10%) are affected and might benefit from the cortisone regime. In the case of a reduction in reoperation less than 50% more than 95% of the study population would take dexamethasone in vain. The surgical procedure has been standardized in order to achieve meaningful statistics.

The national authorities concerned have allowed waiving of particular SAEs, because dexamethasone has been used for decades. Hence, there is a clear understanding of the difference between drug-related and disease-related AEs. Evaluation of secondary objectives will be very lucrative because of the huge sample size. It will offer a refined knowledge of risk factors, the role of co-medication and radiologic findings. Nevertheless, the DRESH study has to clear two hurdles: to be the first RCT to prove significant efficacy for cortisone in the treatment of cSDH in general, and to test a reasonable medication dosage as a relapse prevention for surgical patients in particular.

In the event of significant results a powerful adjuvant therapy in preventing patients from reoperation is offered. For multi-morbid patients with high risk for surgery, a stand-alone therapy with dexamethasone is conceivable.

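### Patients can be removed from the trial after randomisation, for high glucose on drug day 3 or reoperation within 48 hours, with no provision to follow or analyse them

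*Protocol article*

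**What the plan says.** **Glucose.** Under Concomitant care, glucose is evaluated on study day 3, and "At a level higher than 300 mg/dl the patient will be excluded from the trial". Table 2 places this single measurement on day 3 of the drug protocol. The rule removes the patient from the trial and not merely from study drug. The article does not say that follow-up for reoperation continues, or that all randomised patients are analysed as randomised.

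**Early reoperation.** Exclusion criterion 18 is "reoperation within 48 hours after the first operation". The Data analysis section attributes such reoperations to surgical complications and adds: "In such rare cases the patient will be excluded".

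**Timing.** Exclusion criterion 11 rules out "patients for whom study drug cannot be started within 48 hours after evacuation of the hematoma", so dosing begins inside the same 48 hours. Table 2 ticks randomisation in the Screening column. The Methodology section says: "Even patients who undergo emergency surgery can be randomized postoperatively".

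**Endpoint window.** The Abstract and the Primary objective count reoperation within 12 weeks of surgery. The Data analysis section counts it from 48 hours to 12 weeks.

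**The concern.** Randomisation makes the arms comparable at the moment of allocation. A rule that later removes patients because of something the treatment can alter lets treatment decide who is analysed.

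The glucose rule is of this kind. Diabetes is already an exclusion, and the Methodology section says most exclusions relate to dexamethasone or anticoagulants. A very high value on drug day 3 may therefore be a drug effect and occur more often in one arm. Blinding does not prevent this, because the trigger is a laboratory value. If removed patients differ in reoperation risk from those who stay, the comparison is biased. If follow-up stops on day 3, no later definition of the analysis set can recover the missing outcomes.

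The 48-hour rule is an ordinary eligibility criterion for anyone not yet randomised. It becomes a post-randomisation exclusion for a patient who is randomised, perhaps dosed, and then reoperated before hour 48. The document does not rule that sequence out.

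**Working it through.** **Inputs from the Sample size section:** placebo reoperation rate 10%; 5% on dexamethasone (ratio 2); type I error 5%; test "one-sided and based on the score test"; 370 evaluable and 410 randomised per arm; stated power 83%.

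**Inputs the document does not give (assumptions):** k, the share of the dexamethasone arm removed; q, the reoperation risk of those removed. No removals from placebo.

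**Step 1: the plan's own figure.** Normal approximation with pooled variance under the null, 370 per arm, 10% versus 5%:
- pooled rate 0.075; null SE = √(0.075 × 0.925 × 2/370) = 0.01936
- alternative SE = √((0.09 + 0.0475)/370) = 0.01928
- power = Φ((0.05 − 1.645 × 0.01936)/0.01928) = Φ(0.94) = 82.7%

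Full binomial enumeration of the same test gives 83.3%. The stated 83% reproduces as a test against equal rates, so equal rates are the null used below. (The section words its null as a ratio of at most 2; that is a separate point.)

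**Step 2: type I error when there is no true effect.** With 10% in both arms, the rate among dexamethasone patients who remain is (0.10 − k·q)/(1 − k).

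Example, k = 5% and q = 20%: (0.10 − 0.01)/0.95 = 0.0947. With 410 placebo and 410 × 0.95 = 389.5 dexamethasone patients, the null SE is 0.02098 and the alternative SE 0.02097. The rejection probability is Φ((0.00526 − 1.645 × 0.02098)/0.02097) = Φ(−1.395) = 8.2%.

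| Removed (k) | q = 10% | q = 20% | q = 30% |
|---|---|---|---|
| 0.5% | 5.0% | 5.3% | 5.5% |
| 1% | 5.0% | 5.5% | 6.1% |
| 2% | 5.0% | 6.1% | 7.4% |
| 5% | 5.0% | 8.2% | 12.7% |

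Binomial enumeration agrees closely (8.1% and 12.7% at k = 5%).

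**Step 3: direction when the drug works.** With 5% true risk on dexamethasone, k = 5%, and enumeration with 410 versus 390 patients:
- removed patients at the arm's own 5% risk: power 86.0%
- removed patients at 0% risk: observed rate 0.05/0.95 = 5.26%, power 81.8%
- removed patients at 20% risk: observed rate (0.05 − 0.01)/0.95 = 4.21%, power 94.7%

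The bias can therefore favour or penalise dexamethasone.

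**Step 4: the 48-hour sequence.** Criterion 11 requires dosing to start by hour 48. Criterion 18 cannot be fully known until hour 48. Unless every patient starts at about hour 48, criterion 18 cannot be checked in full before the first dose. As written, it can act after randomisation.

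**Step 5: power if early reoperations count.** Assume 1% drug-unrelated early reoperations in both arms, so 11% versus 6% instead of 10% versus 5% (normal approximation, one-sided 5%):
- 400 per arm: 85.2% falls to 81.4%
- 370 per arm: 82.7% falls to 78.7%

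**The case against.** The strongest reply is that the harm is unquantified and may be slight. Diabetics are excluded and glucose is scheduled only once, so a removal rate of 1% or less is at least as plausible as 5%, and the shift is then small. Nothing in the document links glucose to reoperation; with average risk among those removed, type I error stays at 5.0%. This stands as a limit on size. It does not defend the rule, which still discards outcomes on the basis of an on-treatment measurement.

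The 48-hour rule is prespecified, applied under double blinding, justified as surgical and described as rare. Nothing shows unequal losses between arms. That also stands: this is the weaker part, and mainly a matter of clarification.

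Two readings go further than the text allows. One is that early reoperations are primary-endpoint events being thrown away. That holds under the wording of the Abstract and the Primary objective, but the Data analysis section starts the window at 48 hours. The other is that Table 2 flatly contradicts the Methodology section on randomisation. The latter only says patients can be randomised after surgery, and the Screening column also holds procedure-related information, so it need not be strictly preoperative. With a separate Post-procedure column beside it, the timing is ambiguous rather than contradictory.

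The statistical analysis plan, not shown, may define an intention-to-treat set. It could not restore outcomes that the protocol stops collecting.

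**Conclusion.** The point holds as a fault in the rules as written. The glucose rule is a treatment-affected exclusion after randomisation with no stated follow-up. The 48-hour rule can also remove randomised and dosed patients.

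The size is unknown. The calculated range runs from no inflation to roughly 13% type I error. It rests on assumed values of k and q, on removals from the dexamethasone arm only, and on equal true rates. At 1% or less removed, the figure is at most about 6%.

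A reader might infer that sicker patients will leave the dexamethasone arm, that almost all glucose exclusions will fall there, or that the type I error will be 8–13%. The document supports none of these as fact. A drug-related imbalance is plausible, but a higher reoperation risk among those removed is only an assumption, and with a true effect the bias could go either way. The sample size arithmetic is not at fault.

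**What to change.** 1. Whatever the clinical rule on study drug, separate stopping study drug from leaving the trial. Follow every randomised patient for reoperation to week 12 and analyse all in the allocated arm. This takes no position on the glucose threshold or its handling.
2. State one time point for randomisation, after surgery and immediately before the first dose, and align Table 2 with it.
3. Reword criterion 18 as no reoperation before randomisation, so that it can be checked at allocation.
4. Reconcile the endpoint window across the Abstract, Primary objective and Data analysis sections. Keep patients reoperated early after randomisation in the analysis set. Report the endpoint with and without reoperations before 48 hours, with one prespecified as primary. Either choice is defensible.

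**Cost.** Wording, one tick in Table 2, and continued follow-up of a few patients. No larger sample is needed: 410 per arm analysed at 10% versus 5% gives 85.9% power. Patients who stop drug may dilute the effect slightly: if 5% of the arm got no benefit, its rate would be 0.95 × 5% + 0.05 × 10% = 5.25%. If early reoperations are made primary, the loss is nearly 4 points under the 1% assumption, which with only 370 per arm falls below the 80% target.

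### Table 2's day windows for Weeks 4, 12 and 24 equal weeks × 4, so they contradict the visit labels and the 12-week primary endpoint; sites that schedule by days would hold the closing visit 29 to 43 days early

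*Protocol article*

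**What the plan says.** The visit schedule is Table 2 of the protocol article, under Interventions, Concomitant care. That section says the mandated assessments follow this table. Its follow-up columns are headed "Week 4 (16±7 days" and "Week 12 (48±7 days", and the Week 24 column carries 96±7 days.

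The text after the table counts in weeks from surgery: "At weeks 4 and 12 after the operation a CT scan and clinical investigation are performed". It then limits the later visit: "Only in the case of reoperation is another visit necessary as an outpatient at week 24". Footnote 7 makes the Week 12 visit the point at which the site records "any new hospitalizations or surgical procedures (directly or indirectly related to the cSDH) since the first hospital discharge".

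Under Data analysis the endpoint is defined as follows: "The primary endpoint is the rate of reoperation between 48 hours and 12 weeks after the initial evacuation of a chronic subdural hematoma". The abstract and the primary objective also give 12 weeks.

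**The concern.** The week label and the bracketed days in each follow-up column cannot both be followed. The days carry the only stated tolerance (±7), so they are what a site, a monitor or a data system would naturally apply.

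The conflict matters most at Week 12, the last routine contact and the one at which new surgical procedures are collected. If that visit is held near day 48, the article shows no assured route by which a reoperation between the visit and day 84 reaches the database. The Week 24 visit applies only to patients already reoperated. For serious adverse events arising more than 21 days after the study drug ends, footnote 10 says only that they "may be reported to the Sponsor within 24 hours of the investigator´s knowledge of the event, if felt appropriate by the investigators". A late reoperation, for example at another hospital, could go unrecorded.

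A secondary consequence is that, if some sites work by weeks and others by days, the CT and Markwalder data under one visit label would come from different times after surgery. The continuous imaging outcomes are to be modelled with time as the repeated factor.

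**Working it through.** **1. Weeks to days.** The inputs are the three column headings in Table 2; days = weeks × 7.

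| Label | Printed days | Weeks × 4 | Weeks × 7 | Printed window | Contains labelled week? | Shortfall at nominal day |
|---|---|---|---|---|---|---|
| Week 4 | 16±7 | 16 | 28 | 9–23 | No | 12 |
| Week 12 | 48±7 | 48 | 84 | 41–55 | No | 36 |
| Week 24 | 96±7 | 96 | 168 | 89–103 | No | 72 |

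A different day zero does not explain the figures. A shifted origin would give a constant shortfall, but the shortfalls are 12, 36 and 72 days. A table broken in extraction is also unlikely, since all three headings follow the same multiplier.

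**2. Gap before the endpoint closes.** The endpoint runs from day 2 to day 84, which is 82 days.
- Visit at day 55: 84 − 55 = 29 days left, 29/82 = 35% of the period.
- Visit at day 48: 84 − 48 = 36 days left, 36/82 = 44%.
- Visit at day 41: 84 − 41 = 43 days left, 43/82 = 52%.

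**3. The plan's own power.** The inputs, from Sample size, are 10% versus 5%, 370 per arm, one-sided 5%, score test. With mean rate 7.5%, the pooled normal approximation is power = Φ[(0.05 − 1.645 × √(0.075 × 0.925 × 2/370)) / √(0.10 × 0.90/370 + 0.05 × 0.95/370)] = 0.827. Exact enumeration of the score test gives 0.833. Both reproduce the stated 83%, so the sample size calculation is not in question here.

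**4. Illustration of lost events.** The article gives no timing of reoperations, so everything in this step is assumption. Suppose every site uses the printed days, every reoperation after the visit is lost, and the loss is proportionally equal in both arms. With a fraction f captured, the rates become 10% × f and 5% × f, and the formula in step 3 is applied again.

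| Assumed timing of events | Fraction captured (f) | Power |
|---|---|---|
| Uniform, visit at day 48 | (48 − 2)/82 = 0.56 | 60% |
| Uniform, visit at day 41 / day 55 | 39/82 = 0.48 / 53/82 = 0.65 | 54% / 66% |
| Exponential, mean 20 days, visit at day 48 | 0.915 | 79% |
| Exponential, mean 30 days, visit at day 48 | 0.839 | 76% |
| Exponential, mean 45 days, visit at day 48 | 0.764 | 72% |

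The exponential rows use f = (1 − e^(−46/m)) / (1 − e^(−82/m)), where m is the mean in days, counted from day 2 and truncated at day 84.

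With no timing model, a loss of 5%, 10% or 20% of events in both arms gives power of 81%, 79% or 74%.

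**The case against.** The best defence is that this is a conversion slip in brackets. The column labels, the abstract, the primary objective, the follow-up text and the endpoint definition all say 12 weeks, and a sensible site would go by the label. The article condenses a fuller protocol, and the 16/48/96 values may appear only in its table.

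Much of this stands. A reader might infer from Table 2 that the endpoint is in effect cut to about seven weeks. The documents do not support that: the definition under Data analysis is unchanged, and the sample size rests on it. A reader might also infer that the trial has about 60% power. That figure needs every site to use the day counts, every later reoperation to be lost, and events to be spread evenly over days 2 to 84, and the article supports none of the three. If sites were split between weeks and days, the loss could not be applied to the whole trial. Late reoperations might also be recovered from hospital records.

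The contradiction itself remains. The article makes Table 2 the operative schedule, and the conflict sits at the visit that closes ascertainment of the primary endpoint.

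**Conclusion.** The point holds as an internal contradiction that must be corrected. The arithmetic is certain: all three day counts are weeks × 4, and none of the windows contains its labelled week. The consequence is conditional. Where a site schedules by days, the last routine visit falls 29 to 43 days before the endpoint closes, and patients not yet reoperated have no later scheduled visit.

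Any loss of power depends on how many sites do this, how many later reoperations go unrecorded, and when reoperations occur. Under the assumptions shown, the result lies anywhere from 81% (5% of events lost) down to 54% (total loss, even spread, visit at day 41). These figures illustrate sensitivity and are not a forecast. The case for correction rests on the conflict at the endpoint visit and does not need any one of them.

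**What to change.** Reconcile the bracketed days in Table 2 with the stated weeks, so that the windows centre on days 28, 84 and 168. Check whether the full protocol and the CRF carry the same wrong figures, and correct them there too.

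Restoring 84±7 is not enough by itself, because that window opens at day 77 and could still leave up to 7 days of the endpoint period unobserved. The closing ascertainment of reoperation should cover the period through day 84. Either the Week 12 window does not open before day 84, or reoperation status is confirmed at day 84 for any patient seen earlier.

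The cost is three numbers in one table, any matching CRF windows, a note to sites and, under the second option, one status check for patients seen early. The endpoint definition and the sample size need no change on this account.

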#### Secondary objectives

The secondary objectives of the study are as follows: to measure the effect of dexamethasone on clinical outcome by the Markwalder score during a period of 12 weeks after surgery; the impact on radiologic signs of the hematoma, such as thickness, membranes and mass-demanding effect (midline-shift); to evaluate risk factors of the genesis and recurrence of cSDH in a prospective study design; risk of infectious complications, for example, pneumonia, urinary tract infection, ventriculitis, meningitis and encephalitis; dexamethasone-dependent severe psychiatric reactions; and death.

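### New non-serious infections stop being recorded one day after the last dose, although infection risk is a secondary objective with no seriousness limit or time window

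*Protocol article*

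**What the plan says.** The Secondary objectives section of the Protocol article lists "risk of infectious complications, for example, pneumonia, urinary tract infection, ventriculitis, meningitis and encephalitis". It does not restrict these to serious events and gives no window for them. The 12-week period in that sentence belongs to the Markwalder score. Infection does not reappear under Secondary Outcome Measures or Data analysis.

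The recording rules are in Table 2 and its footnotes, under Concomitant care:

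- **Adverse events.** The row is marked at postoperative day 2, at day 3 of drug and until hospital discharge. It is blank at weeks 4, 12 and 24. Footnote 8, attached to the last mark, reads "Reporting of all new AEs up to one day after study drug discontinuation; follow-up of ongoing AEs only thereafter".
- **Serious adverse events.** The row is marked through week 12. Footnote 7 says the week 12 visit is used "to ensure that ongoing AEs/SAEs or new SAEs are followed up/documented", and also to note residence, new hospitalizations and procedures. Footnote 10 makes reporting of new serious events to the sponsor a matter of investigator judgement after "the 21-day follow-up period after study drug discontinuation".
- **Concomitant medication.** There is a mark at week 4, but footnote 2 limits the recording to medication "up to the end of study drug medication".
- **Visits.** The text says: "At weeks 4 and 12 after the operation a CT scan and clinical investigation are performed".

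**The concern.** The objective covers infections of any seriousness, but new non-serious ones are collected for only about a week. Choice of comparator gives dexamethasone a biological half-life of 36 to 54 hours, so a cut-off 24 hours after the last dose falls within one half-life, while some drug effect is still to be expected. A pneumonia or urinary tract infection that starts after that point and does not become serious may never reach the case report form.

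Safety is part of the trial's question. The abstract says the trial tests whether the regimen is safe, and the literature discussion gives a low rate of side effects as part of the main purpose. If late infections are not collected, the reported absolute risk may be too low and there are fewer events with which to compare the arms. An analysis plan can define a window, but it cannot recover events that were never written down.

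**Working it through.** The article states no figure to reproduce here. The check has two parts: the length of each recording window, and whether another route closes the gap.

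**Inputs**
- Six daily doses (Investigational drug).
- First dose on day s after surgery, with s from 0 to 2, because the drug must start within 48 hours (Exclusion criteria, item 11).
- New adverse events to one day after the last dose (footnote 8).
- A 21-day period off drug for serious events (footnote 10).
- Week 12 taken as day 84. Alternatively, the Table 2 column is headed "Week 12 (48±7 days", which gives day 41 to 55 if those are postoperative days (an assumption).

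**Windows**
- Last dose: s + 5.
- Close of new non-serious recording: s + 5 + 1 = s + 6, so postoperative day 6 to 8, or 6 days from first dose.
- End of the 21-day period: s + 5 + 21 = s + 26, so postoperative day 26 to 28, or 26 days from first dose.
- Week 12 from first dose: 84 − 2 = 82 to 84 − 0 = 84 days. On the printed interval: 41 − 2 = 39 to 55 − 0 = 55 days.

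**Comparison, counted from first dose**
- Against the 21-day period: 26/6 = 4.3 times as long; non-serious recording covers 6/26 = 23%, leaving 26 − 6 = 20 days.
- Against week 12 at day 84: 82/6 = 13.7 to 84/6 = 14.0 times; 6/84 = 7.1% to 6/82 = 7.3%.
- Against the printed interval: 39/6 = 6.5 to 55/6 = 9.2 times; 6/55 = 10.9% to 6/39 = 15.4%.

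The first comparison is the most cautious, because serious events after 21 days off drug need not be reported to the sponsor. The other two describe documentation at the week 12 visit.

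**Other routes for a late non-serious infection**
- Week 12 visit: as new events, footnote 7 names serious events, hospitalizations and procedures. Non-serious events are included only if already ongoing.
- Week 4 post-discharge information: its content is not described, and footnote 8 as written allows only follow-up of ongoing events by then.
- Week 4 concomitant medication mark: antibiotics could reveal an infection, but footnote 2 confines the record to drugs taken up to the end of study treatment.
- Neurological worsening: a different type of event.
- Waived SAEs: meningitis, ventriculitis and encephalitis are still entered as serious in the case report form, so they are not part of the gap.

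What remains is mainly non-serious pneumonia and urinary tract infection starting after about day 6 to 8.

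**Scale, by assumption only.** The article gives no infection rate and no onset times. If 1% to 5% of patients had a first non-serious infection after the cut-off, 410 × 0.01 = 4.1 to 410 × 0.05 = 20.5 patients per arm would go unrecorded. If every infection began before the cut-off, none would.

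**The case against.** The strongest reply is that nothing here conflicts. Infection has no stated window, so it can be read as an on-treatment safety objective of a six-day drug, and footnote 8 then fits it. That stands in part: a reader might infer an outright contradiction between the objective and the footnote, and the article does not support one. But the article does not state an on-treatment window either, and the footnote is an explicit stop rule, not a detail left to a fuller document.

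A reader might also infer that serious and non-serious infections will be pooled into one count over unequal periods. No section says so. How infections are counted belongs to an analysis plan that is not shown, so the point rests on what is collected.

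It can be argued that the contrast with serious events is softer than the schedule suggests, given footnote 10, and that the undescribed week 4 items might pick up some infections. Both are fair. The first is why the 4.3-fold comparison leads. The second makes week 4 an uncertain route, not a reliable one.

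Finally, the residue is small and the cut-off is the same in two blinded arms. That also stands, and it limits the consequence without removing it.

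**Conclusion.** The concern holds in a limited form. As written, the plan has no reliable route for a new non-serious pneumonia or urinary tract infection that starts later than one day after the last dose, although infection risk without a seriousness limit is a secondary objective. The absolute infection risk may therefore be understated. The size of the loss cannot be derived from the article, and the percentages of time must not be read as percentages of events missed.

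It would be tempting to conclude that the comparison of the arms is biased. The article does not support that: the rule is identical in both arms, and nothing shows that missed infections would fall unequally. Serious infections, those leading to hospitalization, death and reoperation are unaffected. The day counts assume six consecutive daily doses starting 0 to 2 days after surgery. The point merits a change because uncollected data cannot be recovered and the change is cheap, not because a main result is in doubt.

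**What to change.** Amend footnote 8 and the adverse event row of Table 2 so that new infections of any seriousness are recorded, with type and onset date, at the week 4 and week 12 visits. Compare the arms over one fixed window for serious and non-serious infections alike. First dose to 21 days after last dose is a reasonable example, since footnote 10 already uses that post-drug period. The article gives no infection-specific reason for 21 days, so another fixed length could be justified. Leave other non-serious events at treatment plus one day.

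Both visits are needed. The column headed "Week 4 (16±7 days" gives day 9 to 23, which is 26 − 23 = 3 to 28 − 9 = 19 days before the window closes. If the tolerance were applied to day 28 instead (an assumption), the earliest visit, day 21, would still be up to 28 − 21 = 7 days short. Week 12 closes the window on either reading: its earliest printed day is 41, and 41 − 28 = 13 days after the window ends; at day 84 the margin is 84 − 28 = 56 days.

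The cost is a reworded footnote, two marks in Table 2 and a few case report form items, with no extra visit or test. The downsides are slightly more data entry, a higher reported infection rate in both arms, and reliance on patient recall at week 12 for mild infections after the week 4 visit.

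If the rule is kept, state that the non-serious infection comparison covers only treatment plus one day.
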